#### Data from the online and offline questionnaires on SoBO and SoA

As a subjective counterpart, the data from the questionnaires will be analyzed. The online questionnaire will be repeated in five different timepoints (baseline, 1 min, 2.30 min, 5 min, and 6.30 min): to exclude temporal effect, we will first compare the factors TIME (corresponding to the previously mentioned timepoints where the online questionnaire is administered) and QUESTION (corresponding to the four statements of the online questionnaire) with an ANOVA 5 × 4. We can eventually proceed to an average of the statements across timepoints and then we will compare the four statements (specifically comparing results from “real statements” with “control ones”) and the CONDITION (1PP, 3PP) in an ANOVA 4 × 2. We predict finding higher levels of ownership and agency for the real statements in 1PP, in respect to the control statements and in respect to 3PP.

Concerning the offline questionnaire (administered at the end of every IVR condition), we will analyze the data comparing statements among the two conditions (1PP and 3PP).

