### Trial design

This study is a cross-over (within-subjects) RCT conducted at the Smart-Aging Research Center (Institute of Development, Aging and Cancer, Tohoku University), Sendai City, Miyagi Prefecture, Japan. All participants will perform both experimental and control conditions (in other words, all participants will act as their own controls). This study (version 1.0) was registered with the University Hospital Medical Information Network (UMIN) Clinical Trial Registry (UMIN000034255) on 1 October 2018.

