#### Online and offline questionnaires on SoBO and SoA

We will administer an online questionnaire for the subjective experience of SoBO and SoA. To control for eventual changes in subjective feelings during the intervention at different timepoints (in the middle of the baseline phase [i.e. after 2 min from the beginning if the IVR session], during the intervention at 1 min [i.e. while the avatar is running], at 2.5 min [i.e. while the avatar is slow walking ], at 5 min [i.e. while the avatar is running], and at 6.5 min [i.e. while the avatar is slow walking]), we will ask participants to rate their level of agreement (on a 1–7 Likert scale where 1 means “totally disagree” and 7 means “totally agree”) with respect to four statements: two of them (one is a “real statement” that checks for the actual presence of the illusion, while the other is a “control statement”) about SoBo and the other two about SoA (see Table 1) (see Fig. 2b).

**Table 1 Tab1:** Online questionnaire on SoBO and SoA

s1	SoBO	I feel as if I’m looking at my own body.
s2	SoBO control	I feel as if the virtual body belongs to another person.
s3	SoA	The virtual body moves just as I want, as if I am controlling it.
s4	SoA control	I feel as if the virtual body is controlling my will.

Questionnaire verbally administered during the vHIE (at 5 timepoints, at 2 min from baseline, and 1 min, 2.30, 5 and 6.30 min of vHIE) concerning the subjective participant’s feelings during the intervention. The statements s1 and s2 concern the SoBO, while the statements s3 and s4 concern the SoA. The statements s1 and s3 are “real statements” while statements s2 and s4 are “control statements.” Individuals will rate their level of agreement to the following statements on a 1–7 Likert scale (1 means “complete disagreement” and 7 means “complete agreement”).

Another questionnaire will be administered right after every IVR session (both after 1PP and 3PP intervention conditions) to check details for feelings of movement, motor control, and physical effort (see Table 2) (see Fig. 2 a). The statements are selected and adapted from previous studies [33, 41].

**Table 2 Tab2:** Offline questionnaire on SoBO and SoA

s5	Located	During the experiment, I felt as if my body was located where I saw the virtual body to be.
s6	Ownership	During the experiment, I felt that the virtual body was my own body.
s7	Standing	During the experiment, I felt that I was standing upright.

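### The time check before averaging the online ownership and agency ratings omits CONDITION, so no planned analysis tests whether the 1PP–3PP gap changes over the session

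*Protocol article*

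**What the plan says.** Under *Statistical analysis*, the subsection on the online and offline questionnaires sets out three steps for the online ratings.

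1. The ratings come from five occasions: "The online questionnaire will be repeated in five different timepoints (baseline, 1 min, 2.30 min, 5 min, and 6.30 min".
2. A preliminary check is made: "to exclude temporal effect, we will first compare the factors TIME" and QUESTION, the latter "corresponding to the four statements of the online questionnaire) with an ANOVA 5 × 4". CONDITION is not named.
3. Averaging follows: "We can eventually proceed to an average of the statements across timepoints". Only then are the statements compared together with CONDITION: "and the CONDITION (1PP, 3PP) in an ANOVA 4 × 2".

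The *Measurements* section gives the reason for asking repeatedly: "To control for eventual changes in subjective feelings during the intervention at different timepoints". The *Trial design* section makes clear that each participant rates under both perspectives: "All participants will perform both experimental and control conditions". The prediction for these data is one of level: "We predict finding higher levels of ownership and agency for the real statements in 1PP", relative to the control statements and to 3PP.

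**The concern.** Whether averaging over time is harmless depends on the comparison that follows it. Here that comparison is 1PP against 3PP. Averaging hides something about it when the 1PP–3PP gap appears, grows or fades during the session, which is what TIME × CONDITION and TIME × QUESTION × CONDITION measure. The planned check contains neither term, and no later analysis of the online ratings does. The heart-rate and Stroop ANOVAs in the same section both include CONDITION.

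A gap that changes over time is not far-fetched in this design. The first rating is taken in the familiarization phase, when the avatar stands still; the other four are taken while it runs or walks. The agency statement s3 is about the avatar's movement, so its first rating differs in kind from the rest. The Discussion also expects heart rate to fluctuate with the virtual movements in 1PP but not in 3PP, which is a condition-specific time course in a companion measure.

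At stake is one part of the first-phase manipulation check, which the article uses to judge whether the virtual intervention worked before it turns to the Stroop and fNIRS results.

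**Working it through.** **The plan's own figure.** The protocol gives no power or error figure for this check. Its only such figure, the sample size of 28 (30 recruited), concerns Stroop response time and plays no part here.

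**Cells collected and cells used.** Each participant gives 5 timepoints × 4 statements × 2 conditions = 40 ratings. The planned check has 5 × 4 = 20 cells.

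**Algebra, if the check is pooled over conditions.** Let b1 and b3 be the change in a rating from first to last timepoint in 1PP and 3PP.

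- Pooled drift, seen by the 5 × 4 ANOVA: (b1 + b3)/2
- Change in the 1PP–3PP gap, seen only with CONDITION: b1 − b3

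With independent residuals of SD σ in each condition, the average of the two conditions has SD σ/√2 and the difference has SD √2·σ. Signal relative to noise is therefore (b1 + b3)/(√2·σ) for the pooled check and (b1 − b3)/(√2·σ) for the gap. With σ = 1:

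- +1/−1: 0 against 2/√2 = 1.41
- +1/−0.5: 0.5/√2 = 0.35 against 1.5/√2 = 1.06
- +1/0: 1/√2 = 0.71 for both
- +1/+1: 1.41 against 0

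So the two tests are equally sensitive when only one condition drifts. They part company when both do.

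**Simulation of the ANOVAs.** Assumptions, since the protocol gives no values: n = 30; SD 1.0 between subjects, 0.8 subject-by-condition, 1.0 residual; ratings rounded and limited to 1–7; five equally spaced timepoints; linear drift in s1 and s3; 2000 runs; each term tested at 0.05. The columns show the share of runs in which at least one of two terms was significant: TIME or TIME × QUESTION for the planned check, TIME × CONDITION or TIME × QUESTION × CONDITION for the alternative. With two tests, chance is about 0.10.

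| Drift 1PP / 3PP | (b1+b3)/2 | b1−b3 | Planned 5 × 4 | Terms with CONDITION |
|---|---|---|---|---|
| 0 / 0 | 0 | 0 | 0.11 | 0.10 |
| +1 / −1 | 0 | 2 | 0.09 | 1.00 |
| +0.75 / −0.75 | 0 | 1.5 | 0.10 | 0.99 |
| +1 / −0.5 | 0.25 | 1.5 | 0.28 | 0.99 |
| +1 / 0 | 0.5 | 1 | 0.79 | 0.77 |
| +0.75 / 0 | 0.375 | 0.75 | 0.51 | 0.52 |
| +1 / +1 | 1 | 0 | 1.00 | 0.10 |

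With a +1/−1 drift in s3 alone, the shares were 0.10 and 0.96.

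**Closed-form cross-check for one statement.** Take a 0.5-point rise in 1PP and a 0.5-point fall in 3PP over four steps, residual SD 1, n = 30. The slopes are ±0.5/4 = ±0.125 per step and differ by 0.25. With timepoints coded −2 to 2 the sum of squares is 10, so the standard error of the slope difference is √2/(√10 × √30) = 0.082. The noncentrality is 0.25/0.0816 = 3.06 on 29 df, giving power of about 84%. The pooled slope is exactly zero, so the pooled trend test rejects in 5% of trials, its nominal level.

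**The case against.** Four points can be made for the plan.

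- **The harmful pattern is not predicted.** A reader might infer that opposite courses are to be expected and that a real time effect would then be declared absent. The documents do not support that. The *Interventions* section says the illusion is meant to arise in 1PP and not in 3PP, which suggests a low, flat course in 3PP rather than a falling one, and the analysis section predicts a difference in level. For a drift in 1PP alone, adding CONDITION gains no detection power (0.79 against 0.77). No threshold for averaging is stated either. This objection stands, and it limits the size of the point.
- **Pooling is not stated.** The 5 × 4 ANOVA might be meant once per condition, which would remove the cancellation, and a condensed article may leave that to a fuller document. This stands in part. The article does name the factors and the layout and says nothing of separate runs. Even two separate ANOVAs would not test whether the gap changes.
- **The averaged comparison is sound.** A reader might infer that the 4 × 2 ANOVA would misstate whether embodiment was present. It would not: the mean of the timepoint differences equals the difference of the time-averaged means, whatever the time course. A reader might also infer that pooling treats a participant's two sets of ratings as independent. Nothing in the article says so; the design is within-subject, and averaging a participant's two sessions before a repeated-measures ANOVA is legitimate.
- **The check is one of several.** Heart rate and the offline questionnaire belong to the same first phase and are compared between conditions. All of these are additional outcomes.

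**Conclusion.** The point holds in a limited form. The planned check leaves out the term that bears on the comparison it prepares, and no other planned analysis of the online ratings supplies it.

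Read as pooled over conditions, the check is at about chance level for mirrored drifts, has 0.28 against 0.99 for +1/−0.5, and raises a flag in every simulated run (1.00) for a shared 1-point drift that leaves the gap unchanged. For a drift in 1PP alone there is no material difference in detection, although the pooled check cannot say which condition drifted. These figures rest on assumed SDs, linear drifts and equally spaced timepoints; the algebra behind them does not depend on the SDs chosen.

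The loss is confined to information on when embodiment was present, within a manipulation check. The session-average 1PP–3PP contrast and the primary Stroop analysis are unaffected. The change is worth making because it is free, not because the trial's main conclusion hangs on it.

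**What to change.** Replace the 5 × 4 ANOVA by a TIME × QUESTION × CONDITION (5 × 4 × 2) repeated-measures ANOVA. Inspect TIME × CONDITION and TIME × QUESTION × CONDITION before averaging, and state beforehand what will count as negligible. If these terms are not negligible, report the 1PP–3PP difference at each timepoint alongside the time-averaged result. A time effect common to both conditions need not prevent averaging for the 1PP–3PP comparison.

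If the sponsor intended one 5 × 4 ANOVA per condition, the text should say so, but the terms with CONDITION are still needed to show whether the gap changes.

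The cost is one further factor in an analysis of ratings that are collected anyway, and a sentence or two of wording. No new data, visits or participants are required.

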### Interventions

Participants will visit the laboratory (located in the Smart-Aging Research Center) for two sessions, one week apart, corresponding to the two intervention conditions. In both sessions, the participants sit comfortably on a stool with their feet firmly resting on the ground and their arms relaxed by their sides. They have to wear the Oculus visor (oculus.com), equipped with two lenses that show the virtual world. They will be instructed to keep their bodies still but they can move and rotate their head, to explore the virtual body and the environment. The virtual environment, as well as the virtual bodies and the animations, is modelled in 3D Studio Max 2015 and implemented in Unity3D: it represents an open space with a green floor (simulating a meadow) and a natural-looking illuminated sky, with a visible horizon. Participants will see a gender-matched life-sized humanoid virtual body.

The intervention will be performed in two conditions. The experimental intervention displays the virtual body in 1PP, where the virtual body substitutes and is spatially coincident with the real one; in other words, to observe the virtual body, the participant has to look towards him/herself. The control intervention consists of displaying the same virtual body in 3PP, where the virtual body is collocated approximately 1.5 m to the left of the real participant’s body; in other words, to observe the virtual body, the participant has to rotate his head and look towards his left side.

In both conditions (1PP and 3PP), the intervention starts with a familiarization phase of 4 min (hereinafter baseline) where the gender-matched virtual body is displayed but there is no animation yet (i.e. the virtual body in both 1PP or 3PP is standing still). This phase is necessary to induce the illusory sensation of ownership over the virtual body (in 1PP) or not to induce it (in 3PP) (see the “Measurements” section for the online questionnaire on SoBO and SoA) for the baseline recording of the HR (see the “Measurements” section) and to check for eventual sickness problems due to the virtual display.

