#### Additional outcomes

Additional multiple outcomes are the results obtained during the intervention itself (i.e. HR, online and offline questionnaires), in addition to the TDMS scale results.

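### The online agency ratings may be averaged over five timepoints, one of which precedes any avatar movement. The prior time check only partly guards against this, so the 1PP–3PP agency contrast could be diluted by 0–20%.

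*Protocol article*

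**What the plan says.** The protocol article's statistical section on the questionnaires has the online ratings "repeated in five different timepoints (baseline, 1 min, 2.30 min, 5 min, and 6.30 min"). The Measurements section places the first of these "in the middle of the baseline phase", 2 minutes into a 4-minute familiarization phase. Under Interventions, in that phase "there is no animation yet (i.e. the virtual body in both 1PP or 3PP is standing still"). The other four ratings fall while the avatar is running or slow walking.

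Table 1 lists four statements: s1 and s2 on ownership (real and control), s3 and s4 on agency (real and control). Statement s3 reads "The virtual body moves just as I want, as if I am controlling it".

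The analysis has two steps. First, "to exclude temporal effect, we will first compare the factors TIME" and QUESTION in a 5 × 4 ANOVA. Then: "We can eventually proceed to an average of the statements across timepoints". The averaged ratings go into a comparison of the four statements and "the CONDITION (1PP, 3PP) in an ANOVA 4 × 2". No timepoint is left out of the average. The article states no criterion for going on to the average and no alternative if a time effect appears.

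On rank, the Outcomes section says "Additional multiple outcomes are the results obtained during the intervention itself (i.e. HR, online and offline questionnaires"), together with the mood scale.

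**The concern.** At baseline nothing moves, yet s3 asks about control of movement. The Background section itself attributes the illusory sense of agency to the avatar's movements, so on the protocol's own reasoning the agency manipulation has not properly begun. The plan treats heart rate differently: its baseline is kept apart and used as the reference for subtraction. The questionnaire baseline may instead be pooled with the intervention ratings.

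If 1PP and 3PP differ less in agency before movement than during it, a five-point average understates the difference that the plan predicts. The Statistical analysis section makes interpretation of the cognitive result depend on assumptions checked during the intervention, such as embodiment in 1PP. An understated agency contrast could make the manipulation look weaker than it was.

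**Working it through.** The protocol gives no effect size, variance or power for the questionnaire; its sample-size calculation concerns Stroop reaction time only. There is no figure to reproduce here.

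**Inputs from the document.** Five timepoints, one static and four moving; 30 participants, each rated in both conditions.

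**Assumptions (not in the document).** b = baseline 1PP–3PP agency contrast divided by the contrast D during movement, range 0 to 1. r = common correlation between timepoints of the within-person 1PP–3PP differences, range 0 to 1, with equal variances. Two-sided 5% paired test.

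**Step 1: dilution.** Four-point mean contrast = D. Five-point mean contrast = (4D + bD)/5 = D(4 + b)/5. Relative loss = (1 − b)/5.

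| b | five-point contrast | loss |
|---|---|---|
| 0 | 0.80 D | 20% |
| 0.25 | 0.85 D | 15% |
| 0.5 | 0.90 D | 10% |
| 0.75 | 0.95 D | 5% |
| 1 | D | 0% |

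**Step 2: power.** A fifth rating also reduces noise. The variance of a mean of k ratings is proportional to (1 + (k − 1)r)/k, so the standardised contrast changes by the factor

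q = [(4 + b)/5] × √{[(1 + 3r)/4] / [(1 + 4r)/5]}.

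With n = 30, a standardised contrast of 0.529 on the four moving timepoints gives 80% power (noncentral t, 29 degrees of freedom). The five-point power is that of 0.529 × q:

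| b | r = 1: q, power | r = 0.5: q, power | r = 0: q, power |
|---|---|---|---|
| 0 | 0.800, 61% | 0.816, 63% | 0.894, 71% |
| 0.5 | 0.900, 71% | 0.919, 73% | 1.006, 80% |
| 1 | 1.000, 80% | 1.021, 82% | 1.118, 88% |

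The effect runs from a loss of 19 percentage points to a gain of 8.

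**Step 3: does the TIME × QUESTION ANOVA protect against this?** As worded it has no CONDITION factor. If ratings are pooled over conditions, a drop confined to 1PP is halved before it is tested. A drop of equal size in both conditions could be flagged although it leaves the contrast unchanged (b = 1).

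The check was simulated with assumed values: rating SD 1.5, within-person correlation 0.5 for the same statement, n = 30, ratings averaged over the two conditions, and only the 1PP baseline rating of s3 lowered.

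| drop in 1PP s3 at baseline (points) | TIME × QUESTION significant |
|---|---|
| 0.5 | 11% |
| 1.0 | 38% |
| 1.5 | 80% |
| 2.0 | 98% |

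Suppose the movement contrast is 1 point and vanishes at baseline (b = 0). The drop is then 1 point, and the check misses it in about 100 − 38 = 62% of runs. With a 2-point contrast it misses about 2%.

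**The case against.** The strongest reply is that the averaging is optional and comes after a step meant to rule out time effects. If s3 departs clearly at baseline, that step should show it, and averaging is then not the indicated path. This stands for large departures, as Step 3 shows. It does not stand for departures of about 1 point or less. The step also tests something other than the 1PP–3PP contrast.

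A reader might infer that s3 has no valid answer at baseline and that a fifth of the agency contrast is therefore lost. The document does not support that. Participants are told to keep still, so a still avatar matches a still body, and some may rate control over it meaningfully. The Interventions section links the familiarization phase to the ownership and agency questionnaire, so the baseline rating is deliberate. The baseline contrast is unknown, and 20% is the upper end of a range that starts at zero. Statement s4 does not mention movement, and s1 and s2 can be rated on a static avatar.

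The consequence is also limited. Offline items s8 and s9 cover agency without averaging over time and are compared between conditions. Heart rate is part of the same check, and no stated rule lets a weak online agency result halt the second phase. Dilution towards zero cannot create a false embodiment finding.

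It can also be said that an article need not specify which timepoints are averaged. But this text does set out the five-level comparison and the average across timepoints, so the point concerns a stated method, not an omission.

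**Conclusion.** The point holds as a minor weakness. The plan permits an average that mixes one pre-movement agency rating with four ratings taken during movement, and the preceding ANOVA is only a partial safeguard.

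The possible dilution of the averaged 1PP–3PP agency contrast is 0–20%, given b between 0 and 1; it would exceed 20% only if the contrast were reversed at baseline. The power figures rest on a hypothetical 80% starting point and on assumed correlations, and the detection rates in Step 3 on assumed rating variability. They show the scale of the problem and do not predict this trial's results.

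The consequence is confined to one manipulation check among the additional outcomes. The ownership statements are not in question, and the Stroop comparison is not biased.

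**What to change.** For the agency statements s3 and s4, test for time drift and average over the four vHIE timepoints only (1, 2.5, 5 and 6.5 min), with CONDITION in the drift model so that a change in the 1PP–3PP contrast over time is tested directly. Report the baseline ratings separately; baseline s1 and s2 remain valid as ownership before movement.

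This uses the same data and the same questionnaire schedule. It costs about one sentence in the analysis text, best fixed before the ratings are analysed.

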#### Stroop task’s RT and ER

The second phase of the data analysis concerns the data collected before and after every IVR intervention, i.e. the results necessary to confirm our main hypothesis (the efficacy of IVR training on cognition).

As previously mentioned, in the Stroop task we will include two measurements, RT and ER: the (incongruent – neutral) contrast, which is assumed to represent Stroop interference, will be calculated. Both (RT and ER) will be analyzed by means of a repeated-measures ANOVA with TIME (before, after) and CONDITION (1PP, 3PP) as within-subject factors. As supplementary analysis, we will check for eventual differences between the two sessions considering only the Stroop task before the vHIE (predicting not differences). According to our hypothesis, we predict finding a shorter RT and lower ER after the vHIE in 1PP compared to 3PP.

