### Randomization of interventions

The two intervention conditions will be administered to all participants in two separate sessions (one week apart). Random assignment to the first intervention using an online program (http://www.graphpad.com/quickcalcs/index.cfm) will take place [43]. Each participant is first assigned to a condition non-randomly (the random number generator is seeded with the time and the day). The assignment of each individual is then swapped twice (to make sure it is really random) with the condition assignment of a randomly chosen participant. Half of the participants (15 individuals) will perform the experimental condition first, while the other half will perform the control condition first. The sequence, and with it the assignment to the first intervention condition, is hidden from the researcher that enrolls the participants until the intervention starts to avoid biases; once the intervention begins, the sequence is no longer blinded from anyone.

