These results would contribute on different levels: from a theoretical perspective, this study would be another proof that the illusion of ownership over the virtual body is extremely effective and can be manipulated in order to arise effects on different levels (perhaps motor and cognitive). The simple fact that it is possible to show some effects consequent to the virtual illusion, comparable to the real ones, means the virtual movements are as effective as the actual ones. Our idea is that the SoBO (here the main variable manipulated through the perspective) can drive other aspects, such as motor function, and those, in turn, can drive others, such as cognitive functions. Theoretical models of motor control should clearly state the body and the sense of body ownership as a variable that can significantly affect the resulted action [68, 69].

From a clinical perspective, these results will have interesting applications: as previously mentioned, the intervention presented here can be very useful for sedentary people or those suffering from cardiopathy to start physical activity in a totally safe and entertaining way, or combining cardio or power exercise, and the IVR training, maximizing the efficacy of both on somatic and cognitive terms. In more extreme situations, patients with motor disorders can perform the virtual training but with the same beneficial effects as physical training [70].

However, this study has some limitations. All participants have to repeat the Stroop task four times (before and after the two IVR sessions). This could have a learning effect, or an effect due to the repetition itself, as a negative consequence. To avoid this, we will randomize the order in which the intervention conditions will be administered, but it is still possible to have a repetition effect. Another potential limitation concerns the control conditions of the intervention: several previous studies using IVR exploit the 3PP as a control condition. In some cases, it seems to have a sort of effect, although the reported effect is smaller than the one of the experimental condition. Finally, a difference between the previous study with a similar design and the current one concerns the type of intervention: in Kujach et al. [17], the training consists of a cycling exercise, while in our study we decided on a running exercise in order to be as consistent as possible with other previous studies with similar IVR setup [33].

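### The primary Stroop ANOVA of this two-period cross-over has no sequence or session term, so any difference between sessions in before-after gain goes into the error term and costs power

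*Protocol article*

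**What the plan says.** Under Trial design the protocol article states: "This study is a cross-over (within-subjects) RCT". Under Randomization of interventions it adds: "The two intervention conditions will be administered to all participants in two separate sessions (one week apart". The order is balanced: "Half of the participants (15 individuals) will perform the experimental condition first, while the other half will perform the control condition first".

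The section on Stroop RT and ER gives the primary model for the incongruent-minus-neutral contrast: a "repeated-measures ANOVA with TIME (before, after) and CONDITION (1PP, 3PP) as within-subject factors". No session, period or sequence factor is named there or in any other analysis section. The one related item is supplementary: "we will check for eventual differences between the two sessions considering only the Stroop task before the vHIE (predicting not differences".

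The limitations paragraph of the Discussion says: "All participants have to repeat the Stroop task four times (before and after the two IVR sessions". It continues: "This could have a learning effect, or an effect due to the repetition itself, as a negative consequence". The remedy offered is the randomised order, with a reservation: "we will randomize the order in which the intervention conditions will be administered, but it is still possible to have a repetition effect".

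**The concern.** Balancing the order makes a practice effect average to zero over the two sequences. It does not take that effect out of each participant's data. If the before-after change in interference is larger in the first session than in the second, the 1PP-minus-3PP contrast is pushed one way in participants who start with 1PP and the other way in those who start with 3PP. The cause is known and recorded for every participant, yet a model with only TIME and CONDITION treats the resulting spread as random error.

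What is at stake is mainly power. The trial is sized at 80% power for 28 participants with two to spare, so it has little precision to give away. If the sequences finish with unequal numbers, part of the practice effect also enters the estimate.

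The supplementary check does not help. It uses only scores taken before the virtual exercise, so under any reading it cannot see a difference in before-after gain, and it adds no term to the primary model.

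**Working it through.** **Inputs from the article.** Two sessions; 15:15 allocation; four Stroop administrations; α = 0.05, power 0.8, N = 28, with 30 recruited.

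**The plan's own figure.** N = 28 cannot be reproduced, because the Sample size section calls the effect moderate and gives no number, test, sidedness or correlation. A paired test with d_z = 0.5 needs 34 (two-sided) or 27 (one-sided). A two-sided paired test reaches 80% power at n = 28 when d_z = 0.549. That value is used below as an assumption, so that the comparison starts at the planned power.

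**Set-up.** For each participant let D = (after − before in 1PP) − (after − before in 3PP). The TIME×CONDITION F-test is the one-sample t-test on D. Let τ be the condition effect, let the SD of D within a sequence be 1, and let g be the session-1 minus session-2 difference in before-after change.

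- 1PP-first: mean of D = τ + g
- 3PP-first: mean of D = τ − g

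A shift common to both administrations within a session drops out of D. Speeding common to incongruent and neutral trials has already dropped out of the interference score. Only g remains.

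**Effect on the error term.** With equal sequences the mean of D is still τ and its true standard error is 1/√n. The variance the model estimates, however, has expectation 1 + g²·n/(n−1). At n = 28:

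- g = 0.25: 1 + 0.0625 × 28/27 = 1.065, SD 1.03
- g = 0.5: 1 + 0.25 × 28/27 = 1.259, SD 1.12
- g = 1: 1 + 28/27 = 2.037, SD 1.43

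The reported standard error is therefore about 3%, 12% and 43% too large.

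**Power and type I error, 14:14 completers** (200,000 simulations, two-sided 5%, τ = 0.549):

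| g (SD of D) | Planned: power | Planned: type I error | With sequence term: power |
|---|---|---|---|
| 0 | 80% | 5.0% | 80% |
| 0.25 | 78% | 4.4% | 80% |
| 0.5 | 73% | 2.9% | 80% |
| 1 | 50% | 0.6% | 80% |

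Type I error with the term is 5.0% in every row. If all 30 complete (15:15), planned power is 83%, 81%, 76% and 54%, against 83% throughout with the term.

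**Unequal completion.** The bias of the unadjusted mean is g(n₁ − n₂)/(n₁ + n₂), where n₁ and n₂ are the completers in the 1PP-first and 3PP-first sequences.

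- 15:13: g × 2/28 = 0.07g, or about 0.036 SD at g = 0.5, against an assumed effect of 0.549
- 15:11: g × 4/26 = 0.15g, or about 0.077 SD at g = 0.5

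The sign depends on which sequence loses participants. When the bias works against the effect, planned power at 15:13 is 80%, 76%, 66% and 36% over the same four values of g, and about 80% throughout with the term. Type I error of the planned test stays at or below 5% in all these cases.

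**Cost when g = 0.** Power with and without the term is 80.0% and 80.1% at 14:14, 79.7% and 80.0% at 15:13, and 75.8% and 76.9% at 15:11.

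**The case against.** The strongest reply is that the plan already handles the matter by design. Order is balanced, so the planned estimate is unbiased, and the test errs on the cautious side. The outcome is differenced twice over, so most general practice cancels and g may well be small; at g = 0.25 the loss is 2 power points. The authors also disclose the limitation. All of this stands, and it sets the grade of the point.

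It might also be said that an article leaves model details to an analysis plan. Here, though, the article lists the factors of the primary model and names the threat. The omission of a sequence term is therefore a stated choice, not a detail left open.

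Four stronger readings are tempting, and the documents do not support them:

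- A reader might infer that learning is expected. The article says only that it could occur and remains possible.
- A reader might infer that the primary result would be biased or open to false positives. With the planned balance there is no bias. At 15:13, which needs both budgeted dropouts to come from one sequence, it is 7% of g.
- A reader might infer that predicting no pre-exercise difference contradicts the admitted learning effect. That needs the check to compare first with second session. If it compares before-1PP with before-3PP, as the TDMS section defines its own between-session check, practice averages out over the two orders and the prediction is consistent with learning. The Stroop text does not settle which is meant.
- A reader might extend the point to heart rate and mood. The article raises repetition for the Stroop task only.

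**Conclusion.** The point holds as a matter of precision. The primary model leaves out a factor that the design makes available and that the article's own limitation calls for. If before-after gain differs between sessions, the planned test is conservative and loses power: little at g = 0.25 SD, 7 points at 0.5 SD, and about 30 points at 1 SD (14:14). Bias arises only with unequal completion and is a small fraction of g.

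These figures rest on assumptions: d_z of about 0.55, a range for g that the documents cannot narrow (they give neither a practice effect nor an SD), normal D with equal variance in both sequences, and the same condition effect in both orders. The cancellation of a constant session shift applies to TIME×CONDITION. In a CONDITION main effect or an after-only comparison of 1PP with 3PP, the full session shift would enter. This is a worthwhile and cheap improvement, not an error that must be corrected before the analysis can be trusted.

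**What to change.** Add SEQUENCE (1PP-first / 3PP-first) as a between-subject factor with its interactions, and take the TIME×CONDITION effect from that model with the two sequences equally weighted. Equivalently, compute D for each participant, estimate the effect as (mean of D in 1PP-first + mean of D in 3PP-first)/2, and use the standard error (s_p/2)·√(1/n₁ + 1/n₂), where s_p is the pooled within-sequence SD, on n₁ + n₂ − 2 degrees of freedom.

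A mixed model with session terms and only a participant random intercept is not the same analysis: it tests TIME×CONDITION against a different error term and should not be substituted as if it were.

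Report the pre-exercise Stroop scores by session order (first, second) as a description of practice, and say so in place of the present wording of the check.

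The cost is one degree of freedom, at most about 1 power point if g = 0, and no new data.
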